#### Target group

The impeding and facilitating factors at the level of the target group will be measured via the perception of the G&G professionals. This indirect way is necessary, because the factors at this level relate to possible participants, not to actual participants of the intervention. A sample of all possible participants (in the population) is hard to delineate. Therefore, the professionals will be asked to answer the questions of the target group level. The professionals will well be able to give an estimation of the impeding and facilitating factors that possibly play a role for older adults to participate (or not) in the G&G interventions, due to their large experience with the target group. The predefined factors of the theoretical framework at the level of the target group are thus translated into questions to be answered by the professionals. For example, the factor “awareness of benefits” is translated into the question: “Do you think older adults understand the benefits of participating in the G&G interventions?” The questions contain six answer categories ranging from (0) ‘not at all’ to (5) ‘completely’.

#### Professionals

The impeding and facilitating factors at the level of the professionals will be assessed by means of digital questionnaires. All professionals who have been trained and certified as G&G coach and/or G&G teacher will be invited to fill out the questionnaire. The predefined factors of the theoretical framework at the level of the professionals are translated into one or more questions per factor. For example, the factor “ownership” is translated into the question “To what extent do you feel responsible for G&G intervention start-up?” Each question contains six answer categories ranging from (0) ‘not at all’ to (5) ‘completely’.

#### Organizations

The impeding and facilitating factors at the level of the organizations will be measured by means of a telephone interview with the managers. The predefined factors of the theoretical framework at the level of the organization are translated into one or more questions per factor. For example, the factor “staff capacity” is translated into the question “Is your staff capacity sufficient to spend time on integrating the G&G interventions in routine practice?” The questions contain six answer categories ranging from (0) ‘not at all’ to (5) ‘completely’.

#### Financial-political context

The impeding and facilitating factors at the level of the financial-political context will also be measured by means of a telephone interview with a strategic or financial local policymaker. The predefined factors of the theoretical framework at this level are translated into one or more questions per factor. For example, the factor “added value” is translated into the question “To what extent do you think that the G&G interventions add something to the existing services for older people in your community?” The questions contain six answer categories ranging from (0) ‘not at all’ to (5) ‘completely’.

### Data analysis

All data will be imported in SPSS statistics 20. Descriptive analysis will be used to characterize use, time to initial use (pace), extent of use (performance) and the intention to continue use beyond the timeframe of the study (prolongation). Data collected at the four stakeholder levels will be merged and aggregated. Intra-class correlations will be calculated to assess the reliability of individual data aggregated at group levels in hierarchical models (i.e. professionals nested in organizations). The relevance of applying multilevel modeling to the data will be assessed by testing an unconditional or null model in which no predictors are specified. Only when significant variations in the dependent variables are present across organizations or municipalities, multilevel regression modeling will be applied. If no significant variation in use, pace, performance or prolongation is found across organizations or municipalities, we confine to single-level modeling techniques.

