Historically, the focus of most studies has been on the individual level of the professional who is expected to change his routine in a way that enables the use of the new EBP [24]. Recently, a growing number of studies also encompass factors at the organizational and the financial-political level [25, 26]. A serious problem of these studies is, however, that the design and statistical methods are not fit to capture the complex interplay between phenomena at the several different hierarchical levels [15]. For example, self-efficacy (individual professional level), positive work climate (organizational level), and funding (financial-political context level) have been identified as important facilitating factors to EBP-use [23]. But, as of yet, it is not known which of these factors is decisive with respect to EBP-use in the presence of the other two. Answers to this type of questions can only be found when factors at more than one stakeholder level are assessed simultaneously, and when the nested data are analyzed employing multilevel modeling techniques.

The overall aim of the study is to identify the determinants of successful implementation of the G&G interventions. The concrete objectives of the study are, first, to describe the variation in actual use between organizations, expressed in terms of pace, performance and prolongation. And, second, to explain this variation at consecutive time points in the process by analyzing the factors at four hierarchical stakeholder levels (i.e. target group, professionals, organizations and financial-political context).

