**Figure 2 Fig2:**
[figure not shown]
Hierarchical stakeholder levels.

The first group (i.e. the target group) consists of the older adults at risk of becoming vulnerable. The second group are the trained professionals, who deliver the G&G interventions. The third group consists of the managers of the participating organizations. When organizations have multiple management-layers, the manager who is closest to the work floor will be invited to act as key-informant. The fourth and final group consists of key informants at the level of the financial-political context. These are local policymakers who are well informed on the execution of the Social Support Act. They will be invited to act as informants for our study.

Based on experiences from an earlier pilot-implementation of the G&G interventions, it is feasible to include at least 15 new organizations in a period of 12 months [35]. Counting with 15 organizations, the sample size at the organizational and financial-political level will be 15 managers and 15 local policymakers. With a minimum of two G&G professionals per organization, the sample size at the professional level will be at least 30 G&G professionals.

With respect to the reach of the target group, concrete performance goals are communicated with the G&G professionals. Each G&G coach is expected to deliver the G&G home visits to at least three older adults (15 G&G coaches × 3 home-visits × 1 participant = 45 participants) and each pair of G&G teachers is expected to deliver at least three group courses, with an average of ten older adults per course (15 G&G teacher pairs × 3 group-courses × 10 participants = 450 participants). In the 2-year period of the data-collection, the sample size at the level of the target group will thus amount to approximately 495 older adults. Taking into account a drop-out rate of 8% [36] a maximum number of 400 older adults participating in the G&G interventions is expected to be feasible.

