## Discussion

The aim of the study described in this protocol is to identify the determinants of successful implementation of the G&G interventions. In this study, health and social care organizations are considered to be part of multilevel functional systems [37], in which factors at different hierarchical levels can impede or facilitate the actual use of the G&G interventions. By assessing the unique contribution of target group, professional, organizational and financial-political context factors, as well as the complex interplay between these factors, results are expected to be of added value to the current scientific knowledge on barriers and facilitators to EBP-use.

The study has several strengths. The first is that implementation success in this study is not only assessed by the parameter use (yes/no), but it is also specified in three other indicators of use, namely: pace, performance and prolongation. This approach yields a much more specified insight in the various aspects of implementation success. Second, the possible factors that are considered in this study are theoretically supported by the Fleuren model, which provides a solid basis and prevents an ad hoc selection of possible factors. Finally, the analyses of the complex interplay between factors at different hierarchical stakeholder levels are executed with advanced multilevel modeling techniques. This is the optimal way of doing justice to the multi-layered nature of reality in implementation processes.

In conclusion, globally [38] and nationally [39] there is momentum to invest in EBPs that support aging individuals to live full, enriching and productive lives for as long and as much as possible. The G&G interventions are an example of such EBPs. They have been designed and tested in the last decade. Now it is time to increase our understanding of how to transport them to health and social care settings in a sustainable way. Identifying the determinants of successful implementation of the G&G interventions will also contribute to the development of ecologically valid implementation strategies of the G&G interventions and comparable new evidence-based practices.

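### A low-power significance test on the null model decides whether clustering by organization is modelled, although the nesting is part of the design and the protocol presents multilevel modelling as its central method

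*Protocol article*

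**What the plan says.** The Data analysis section plans descriptive statistics for all four success parameters, then intra-class correlations, then a check made by "testing an unconditional or null model in which no predictors are specified". The result of that check is binding: "Only when significant variations in the dependent variables are present across organizations or municipalities, multilevel regression modeling will be applied". The opposite branch is also spelled out: "If no significant variation in use, pace, performance or prolongation is found across organizations or municipalities, we confine to single-level modeling techniques". The article gives no significance level, type of test, expected ICC or power for this check.

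Other sections carry no such condition. The Background says that questions about the interplay of levels can be answered only if factors at more than one level are assessed together "and when the nested data are analyzed employing multilevel modeling techniques". The Discussion lists as a strength that "the analyses of the complex interplay between factors at different hierarchical stakeholder levels are executed with advanced multilevel modeling techniques". The Abstract also announces multilevel analysis without qualification.

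On sample size, the Study sample section holds that "it is feasible to include at least 15 new organizations in a period of 12 months", and adds: "With a minimum of two G&G professionals per organization, the sample size at the professional level will be at least 30 G&G professionals". It also counts 15 managers and 15 local policymakers. Under Procedure and measures, implementation success is assessed per organization. Prolongation is a single 0-3 item put to each professional, manager and policy informant.

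**The concern.** Professionals share an organization by design. Whether their answers are correlated is a matter of degree to be estimated. With few organizations and few respondents in each, a non-significant variance component mostly reflects low power and is weak evidence of independence. The rule nevertheless takes it as licence to treat colleagues as independent.

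Two things are at stake. First, when the test misses real clustering, standard errors for organization-level and policy-level factors are too small. Second, the method that the protocol gives as its reason for doing the study may be abandoned because of sampling noise, so the Data analysis section does not deliver what the Abstract, Background and Discussion promise.

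**Working it through.** **Inputs from the article.** Organizations k = 15 (a minimum). Professionals per organization m = 2 (a minimum), so 15 × 2 = 30, which reproduces the stated figure. For prolongation, 2 professionals + 1 manager + 1 policymaker gives about m = 4 answers per organization.

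**Assumptions.** Significance level 0.05; ICC from 0.1 to 0.5; balanced data; a normal outcome as an approximation to the 0-3 item; all respondents in an organization equally correlated; the exact one-way random-effects F test as the null-model test.

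**Power.** With ρ for the ICC, power = P[ F(k−1, k(m−1)) > Fcrit × (1−ρ)/(1+(m−1)ρ) ].

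- m = 2: df 14 and 15, Fcrit = 2.424. At ρ = 0.2 the threshold is 2.424 × 0.8/1.2 = 1.616, and power is 18%.
- m = 4: df 14 and 45, Fcrit = 1.918. At ρ = 0.2 the threshold is 1.918 × 0.8/1.6 = 0.959, and power is 51%.

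| ICC | Power, m = 2 | Power, m = 4 |
|---|---|---|
| 0.1 | 10% | 23% |
| 0.2 | 18% | 51% |
| 0.3 | 31% | 76% |
| 0.5 | 65% | 97% |

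Power reaches 50% at an ICC of about 0.42 for m = 2 and about 0.20 for m = 4.

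**Sensitivity.** Other common tests are weaker at 15 × 2. At ICC 0.1, 0.3 and 0.5, a Wald test at 1.96 has power 1%, 7% and 27%, and a likelihood-ratio test against an uncorrected chi-square(1) has 6%, 21% and 54%. A 10% level raises the F test to 18%, 45% and 78%. More data help only partly: at ICC 0.1, 0.2 and 0.3, power is 16%, 35% and 58% for 15 × 3, and 13%, 29% and 51% for 30 × 2.

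**Type I error for an organization-level factor.** This was simulated with 40,000 data sets per setting and no true effect. The single-level test is ordinary regression on all answers. The clustered test uses organization means with 13 df. The rule as written uses the clustered test after a significant F test and the single-level test otherwise.

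| m | ICC | Single-level, given a non-significant test | Rule as written | Always clustered |
|---|---|---|---|---|
| 2 | 0.1 | 5.5% | 5.4% | 4.8% |
| 2 | 0.2 | 6.3% | 6.0% | 5.0% |
| 2 | 0.3 | 7.0% | 6.4% | 5.0% |
| 2 | 0.5 | 8.5% | 6.4% | 5.2% |
| 4 | 0.1 | 6.7% | 6.4% | 5.1% |
| 4 | 0.2 | 8.2% | 6.5% | 5.1% |
| 4 | 0.3 | 8.9% | 6.2% | 5.3% |
| 4 | 0.5 | 10.4% | 5.1% | 5.0% |

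The 10.4% is imprecise. It rests on the 2.7% of data sets with a non-significant test, about 1,080 of 40,000. A repeat with 600,000 data sets gave 9.7%, so the range for m = 4 is best read as about 7% to 10%.

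**Use, pace and performance.** These are assessed per organization. If each has one value per organization, then m = 1 and the within-organization df are k(m−1) = 15 × 0 = 0. The organization-level null model then cannot separate the two variances, and the power figures above do not apply to these outcomes.

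**The case against.** The strongest defence is that the rule works largely as intended. When clustering is strong, the test finds it and the multilevel model is used; when the test misses, clustering is usually mild. The simulation bears this out, with overall error at or below about 6.5%. A reader might infer serious inflation from the error of ignoring clustering throughout, which at two respondents and ICC 0.5 is 11.5%. The protocol does not plan that analysis. The largest conditional figure for four respondents arises in under 3% of data sets.

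A reader might also infer that the test will nearly always miss clustering. That holds for two respondents at any ICC below about 0.42. Prolongation is asked of about four people per organization, however, and there it holds only below about 0.20. The article does not say that prolongation is analysed in professionals alone. Fifteen and two are also minimums.

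A third tempting reading is that the protocol itself calls single-level analysis unfit. The Background applies that judgement to the design and methods of earlier studies. Its claim that answers require multilevel modelling is still in plain tension with a rule that may discard it.

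Finally, the first objective, describing variation between organizations, is not gated. The descriptive analyses and the ICCs are planned whatever the test shows.

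All of this limits the size of the harm. None of it gives a reason to choose the model by a test this weak.

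**Conclusion.** The concern holds in a limited form and should be fixed. The Data analysis section makes multilevel modelling conditional on a test that, at the minimum sample, more often than not misses an ICC below about 0.42 with two respondents per organization, or below about 0.20 with four. After a non-significant test, the single-level test of an organization-level factor has a type I error of about 5.5% to 8.5% with two respondents and about 7% to 10% with four. Over the whole rule the error is about 5% to 6.5%, so the inflation is modest. The more important defect is that the stated central method can be lost on an uninformative result, contrary to the Abstract, Background and Discussion.

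The conclusion covers prolongation and any other outcome with several respondents per organization. It does not extend these figures to use, pace and performance; if those have one value per organization, the organization-level check is undefined for them. The numbers rest on the assumed level, ICC range, F test, normal outcome and minimum sample.

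**What to change.** Delete the two sentences that make the model depend on significance, and replace them with three commitments:

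- For outcomes with several respondents per organization, always account for clustering by organization, whatever the estimated variance. Either a random intercept with a small-sample correction or an analysis with the organization as the unit of error would serve. Choose a model suited to the 0-3 prolongation item.
- Analyse outcomes that have one value per organization at organization level.
- Report the ICC with a confidence interval as description only.

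No new data are needed. The cost is slightly wider intervals when the true ICC is near zero. With one organization-level factor and the organization as the unit of error, the 95% critical value is 2.160 (13 df), against 2.048 (28 df) for 30 answers treated as independent and 2.002 (58 df) for 60. The ratios are 2.160/2.048 = 1.05 and 2.160/2.002 = 1.08, so intervals are about 5% to 8% wider.

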## Discussion

The aim of the study described in this protocol is to identify the determinants of successful implementation of the G&G interventions. In this study, health and social care organizations are considered to be part of multilevel functional systems [37], in which factors at different hierarchical levels can impede or facilitate the actual use of the G&G interventions. By assessing the unique contribution of target group, professional, organizational and financial-political context factors, as well as the complex interplay between these factors, results are expected to be of added value to the current scientific knowledge on barriers and facilitators to EBP-use.

The study has several strengths. The first is that implementation success in this study is not only assessed by the parameter use (yes/no), but it is also specified in three other indicators of use, namely: pace, performance and prolongation. This approach yields a much more specified insight in the various aspects of implementation success. Second, the possible factors that are considered in this study are theoretically supported by the Fleuren model, which provides a solid basis and prevents an ad hoc selection of possible factors. Finally, the analyses of the complex interplay between factors at different hierarchical stakeholder levels are executed with advanced multilevel modeling techniques. This is the optimal way of doing justice to the multi-layered nature of reality in implementation processes.

In conclusion, globally [38] and nationally [39] there is momentum to invest in EBPs that support aging individuals to live full, enriching and productive lives for as long and as much as possible. The G&G interventions are an example of such EBPs. They have been designed and tested in the last decade. Now it is time to increase our understanding of how to transport them to health and social care settings in a sustainable way. Identifying the determinants of successful implementation of the G&G interventions will also contribute to the development of ecologically valid implementation strategies of the G&G interventions and comparable new evidence-based practices.

## Abbreviations

G&G: GRIP&GLEAM [Dutch: GRIP&GLANS]; GRIP stands for the ability to adapt and self-manage. GLEAM stands for well-being and the feeling that life is good and worth living
EBP: Evidence Based Practice; a practice that has been established as effective through scientific research according to a set of explicit criteria
